## Methods/Design

### Study hypothesis

Participants who eat a nutrition-adequate breakfast will have better cognitive performance than those who eat a nutrition-inadequate breakfast or do not eat breakfast.

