### Sample size calculation and participants

In a related study, the average cognitive performance value of people who ate a nutrition-adequate breakfast, a nutrition-inadequate breakfast and no breakfast has been found to be 36.6, 25.9 and 26.8, respectively [20]. Using these results as reference values, in this study, power is set at 0.8, SAS programming was used, and the necessary sample size was calculated. According to the SAS procedures described by Hu [21], we calculated the sample size as 117 in one city. If the dropout rate is 10%, a total of 130 participants will be needed. Given that the participants will be divided into three groups, and to achieve equal group sizes, 44 participants will be needed for each group. Therefore, 132 participants will be needed for the three groups to include an equal number of men and women in one city. Because this study will be conducted in two cities, 264 total participants will be recruited.

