### Analysis strategy

Statistical analyses will be conducted using SAS 9.2 (SAS Institute Inc., Cary, NC). Descriptive statistics will be calculated for all the variables under examination. Anthropometric measurements at baseline will be analysed to examine the influence of the factors on breakfast behaviour by using multivariate regression analysis, with age, sex, income and education level included in the model. Repeated-measures analysis of variance (ANOVA) will be used to examine cognitive function performance, with breakfast condition (Group A, Group B, or Group C) as the within-subjects variable and sex as the between-subjects variable. Significant confounding variables (in addition to gender), including satiety, mood score before the cognitive function tests, and time between breakfast and the first cognitive function test, will all be included initially as covariates in the two-way ANOVA. The significance level will be set at <0.05. The Bonferroni adjustment method will be used to perform the pairwise comparisons across different breakfast types. The significance test level will be ɑ' = 0.01667 (0.05/3). A modified t-test for gender differences will be used, and the significance level will be set at <0.05. All *P*-values will be two-tailed.

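### Single-step Bonferroni at 0.05/3 for the three breakfast pairs is valid but needlessly conservative; Holm keeps the same 5% family-wise error and loses no rejection

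*Protocol article*

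**What the plan says.** Under Analysis strategy, the global analysis is fixed first: "Repeated-measures analysis of variance (ANOVA) will be used to examine cognitive function performance", with the three breakfast conditions as the within-subject factor. The general level follows: "The significance level will be set at <0.05". For the pairs, "The Bonferroni adjustment method will be used to perform the pairwise comparisons across different breakfast types", and the per-pair level is given as "0.01667 (0.05/3"), that is, 0.05 divided by three. All "values will be two-tailed". No step-down or closed procedure is named, and no sentence says that the pairwise tests depend on a significant ANOVA.

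Under Study hypothesis, those who eat the adequate breakfast "will have better cognitive performance than those who eat a nutrition-inadequate breakfast or do not eat breakfast". The Discussion part of the Abstract makes the same prediction against both comparators jointly.

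Under Sample size calculation and participants, mean performance in a related study for adequate, inadequate and no breakfast "has been found to be 36.6, 25.9 and 26.8, respectively". Power is 0.8 and the result is 117 per city before dropout. No SD, within-subject correlation or alpha is stated for that calculation.

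**The concern.** Two of the three pairs carry the hypothesis: adequate versus inadequate, and adequate versus none. Full support needs both. Single-step Bonferroni loses most on this joint result, because the second contrast must still pass 0.01667 even when the first has clearly succeeded.

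Holm tests the smallest p-value at 0.05/3, the next at 0.05/2 and the last at 0.05, stopping at the first failure. Any p-value below 0.05/3 therefore still leads to rejection, and others may be added. Family-wise error stays at or below 5% without a global test or sphericity; only valid pairwise p-values are needed.

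With exactly three conditions a second route exists. If any two pairwise nulls are true, so is the third, so the only intersection hypothesis is the global null. A valid global test at 0.05 covers it, and each pair may then be tested at 0.05 (closed testing). What is at stake is power for the central claim, not validity.

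**Working it through.** **The plan's own figures.** 0.05/3 = 0.016667, which matches 0.01667. 117/(1 − 0.10) = 130; 44 × 3 = 132; 132 × 2 = 264. All reproduce.

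**Inputs.** Means 36.6, 25.9 and 26.8, so differences of 10.7 (adequate − inadequate), 9.8 (adequate − none) and 0.9 (none − inadequate). N = 117 evaluable per city, or 2 × 117 = 234 pooled. Two-sided tests.

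**Assumption: SD.** It is not given, so N = 117 can be neither confirmed nor refuted. Solving back for the SD that gives 80% power gives about 14.5 to 16.7 if the 117 are treated as three parallel groups of 39, and 25.5 to 29.1 if all 117 contribute to every condition, depending on alpha. The case below takes 29.1, from the repeated-measures F test at 0.05:

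- Grand mean = 89.3/3 = 29.77. Sum of squared deviations = 46.69 + 14.95 + 8.80 = 70.4.
- Noncentrality = 117 × 70.4/29.1² = 9.73 on 2 and 232 degrees of freedom. Power is about 80%.
- Standard error of a pairwise difference = 29.1 × √(2/117) = 3.80. The two main contrasts are 10.7/3.80 = 2.8 and 9.8/3.80 = 2.6 standard errors, against two-sided normal critical values of 2.394 at 0.01667 and 1.960 at 0.05.

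**Power to show both adequate-breakfast contrasts** (simulation under sphericity with the reference means):

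| N | Residual SD | Bonferroni | Holm | Closed (F at 0.05, then pairs at 0.05) |
|---|---|---|---|---|
| 117 | 15 | 99.4% | 99.7% | 99.8% |
| 117 | 20 | 87.9% | 91.2% | 94.8% |
| 117 | 25 | 63.6% | 69.9% | 79.1% |
| 117 | 29.1 | 45.0% | 51.4% | 62.9% |
| 117 | 40 | 17.8% | 22.2% | 31.9% |
| 117 | 50 | 8.8% | 11.6% | 18.5% |
| 234 | 29.1 | 85.9% | 89.4% | 93.7% |

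At N = 117 and SD 29.1 the gain is 51.4 − 45.0 = 6.4 points for Holm and 62.9 − 45.0 = 17.9 points for closed testing. The Bonferroni column is the same, to simulation error, with or without a significant ANOVA required first. A repeat run gave 44.8%, 51.3% and 62.9% for the SD 29.1 row at N = 117.

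**Single contrasts, N = 117, SD 29.1** (adequate versus inadequate / adequate versus none): Bonferroni after the ANOVA 65.4% / 56.4%; Holm 68.2% / 60.5%; closed 74.3% / 68.5%. The chance of at least one rejection is 77.3% for both ungated Bonferroni and Holm, so Holm adds only second and third rejections.

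**Error rates.** Family-wise error under the global null: Bonferroni 4.3%, Holm 4.3%, closed 5.0%. If inadequate and no breakfast are truly equal and the adequate effects are large enough to be always detected, the false-positive rate on that pair is 1.7%, 5.0% and 5.0%. With moderate effects (adequate better than both by 0.297 residual SD, 237 completers) it is 1.7%, 3.8% and 5.1%. In no simulated trial did Holm lose a Bonferroni rejection.

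**The case against.** The strongest reply is that this is a preference. The plan names a valid procedure in advance, computes its level correctly and states that tests are two-tailed. That stands: nothing here is an error or a contradiction. But Holm does at least as well in every data set at the same family-wise level and with no extra assumption, so the change is more than taste.

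A reader might infer that Bonferroni buys nothing in error control. The figures do not support that. On a truly null inadequate-versus-none pair its false-positive rate is 1.7%, against about 4–5% under the alternatives. All stay within the 5% family-wise limit, but Bonferroni is stricter on the single pair.

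It also keeps tests and intervals in agreement. Its matching interval is 1 − 0.05/3 = 98.33%. In the 0.297 SD scenario, at least one pair would be declared significant with a 98.33% interval covering zero in about 8% of trials under Holm and 17% under closed testing. That is a legitimate reason to keep Bonferroni.

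A reader might also infer that the planned ANOVA already gates the pairwise tests. That rests on the order of the sentences only. Against ungated Bonferroni, closed testing loses a rejection in a small fraction of simulated trials (about 0.1–0.3%), and it needs a valid global repeated-measures test. The case for Holm depends on neither.

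Finally, if success strictly requires both contrasts, each may be tested at 0.05 with no adjustment. The hypothesis section joins the comparators with *or*, the Abstract with *and*, and the plan tests all three pairs, so that reading is not settled. Holm serves under either.

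**Conclusion.** The point holds as an optional improvement of low severity. For the three breakfast pairs within one outcome, Bonferroni at 0.01667 is valid but needlessly conservative for a hypothesis that the adequate breakfast beats both other conditions, and Holm is the cleaner choice.

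The size is not fixed by the document. With the reference means, power for both contrasts rises by about 6 points with Holm at N = 117 and SD 29.1, by about 3 points at SD 20, by about 3.5 points with 234 pooled at SD 29.1, and by almost nothing at SD 15. Closed testing gains more (about 18, 7 and 8 points in the first three cases) but on extra conditions. These figures rest on the assumed SD, the reference means and sphericity; that Holm never loses a Bonferroni rejection rests on none of them.

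A large, certain loss of power should not be inferred, because the protocol gives no SD from which to establish one. Nor does the point extend to multiplicity across the several cognitive outcomes: the family here is the three pairs only.

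**What to change.** In Analysis strategy, replace the fixed 0.01667 by wording such as: within each outcome, the three pairwise breakfast comparisons will be tested by Holm's procedure at a two-sided family-wise level of 0.05, comparing the ordered p-values with 0.0167, 0.025 and 0.05 and stopping at the first that is not significant.

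Optionally, state that pairwise tests proceed only after a significant repeated-measures ANOVA at 0.05, with sphericity holding or corrected for; each pair may then be tested at 0.05. Choose one route before the data are seen.

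Keep 98.33% intervals for estimation and say that they may not match the test decisions. The cost is one or two sentences, with no added participants, visits or data. The price is the higher false-positive rate on inadequate versus none, within the 5% cap, and occasional disagreement between a test and its interval.

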## Discussion

According to the design of the experiment, all the participants will receive three breakfast treatments in different stages to determine whether differences in cognitive function exist among the different groups. This experimental design will ensure that there is a balance in the confounding variables in each group and will eliminate the bias caused by participants’ characteristics. In addition, to ensure consistency in the composition and quality of the breakfast conditions, the same breakfast recipes will be used in the two cities, and one breakfast company will be responsible for the production and the distribution of the different breakfasts. In addition, breakfast samples will be sent to the Chongqing Food and Drug Inspection Institute for the measurement of energy and composition.

One challenge that we will face in this study will be the dropout rate and participant compliance. Participants will need to be present for three consecutive weeks. Some participants might fail to complete the entire study because of business travel, tardiness, resignation and other reasons. We will fully explain the principles and requirements to the participants before the study begins to ensure compliance.

The present study will have both strengths and weaknesses. This will be the first investigation of the associations among breakfast quality and energy and cognitive function among adult white-collar workers in China. The sample size will provide sufficient power to detect relatively small effects. It is expected that a high-quality breakfast will improve short-term cognitive function, whereas a low-quality breakfast will reduce short-term cognitive function. Furthermore, baseline information on the general demographic characteristics (including age, gender, marital status, education level, occupation, smoking habits, and drinking habits), frequency of breakfast eating, and body composition will be collected. More than 260 blood samples from participants will be tested, thus providing sufficient power to explore the effects of blood glucose on cognitive function. In addition, satiety and mood will be measured to address some of the potential confounding variables in this study. One limiting factor is the type of cities that were selected in this study, because China is very large. Additionally, there are various types of breakfasts with diverse nutritional values. In this study, we will restrict our analysis initially to Chongqing and Shenyang only, noting that imposing certain constraints to represent them as being nationally representative would be restrictive.

In summary, “breakfast”, which is derived from the combination of “break” and “fast”, is primarily consumed after a restful night of voluntary starvation. Individuals wake up requiring immediate nourishment and “break” their “fast” by consuming the first and most important meal of the day, and breakfast must provide sufficient nutrition for optimal physiological health and physical wellbeing of the body throughout the day. The effects of a healthful breakfast as observed through enhanced cognitive function would validate our hypotheses of the importance of breakfast and might prompt public health officials to begin to focus on health education regarding the value of eating a nutritious breakfast.

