### Participants and study design

Participants will be recruited from two cities, Shenyang and Chongqing, China. Shenyang is located in northeast China, whereas Chongqing is located in southwest China.

The inclusion criteria will be: white-collar workers aged 25–45 years involved mainly in office work, who engage in brain work and are amenable to skipping breakfast.

The exclusion criteria will be: individuals with mental illness, oral disease or other severe diseases; pregnant women and nursing mothers; individuals who have a tendency to lose weight; and individuals who never eat breakfast.

This crossover study will last for three weeks. Participants will be randomly assigned to one of three groups (Group A, Group B, and Group C). In the first week, Group A will be provided with a nutrition-adequate breakfast, Group B will be provided with a nutrition-inadequate breakfast, and Group C will be provided with no breakfast. Each participant will complete tests of blood glucose level, mood, hunger and satiety, and cognitive function. In the second week, Group A will be provided with no breakfast, Group B will be provided with a nutrition-adequate breakfast, and Group C will be provided with a nutrition-inadequate breakfast. Each participant will complete blood glucose level, mood, hunger and satiety, and cognitive function tests. In the third week, Group A will be provided with a nutrition-inadequate breakfast, Group B will be provided with no breakfast, and Group C will be provided with a nutrition-adequate breakfast. The blood glucose level, mood, hunger and satiety, and cognitive function will be tested again. All participants will take the tests in three successive weeks, and each participant will be tested in three breakfast treatments: nutrition-adequate breakfast, nutrition-inadequate breakfast, or no breakfast. The study design is presented in Fig. 1.

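### The named repeated-measures ANOVA in its standard form drops anyone who misses one of three weeks, though missed attendance is foreseen; a mixed model on all attended visits would keep these data

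*Protocol article*

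**What the plan says.** Under Participants and study design, each person attends once a week and receives each breakfast condition once: "All participants will take the tests in three successive weeks, and each participant will be tested in three breakfast treatments".

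Under Analysis strategy, one method is named for the cognitive outcomes: "Repeated-measures analysis of variance (ANOVA) will be used to examine cognitive function performance, with breakfast condition" as the within-subjects variable and sex as the between-subjects variable. Pairwise breakfast comparisons are tested at 0.05/3 = 0.01667. Satiety, mood and time since breakfast are listed as covariates.

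Under Sample size calculation and participants, the base figure is stated as "we calculated the sample size as 117 in one city", followed by "If the dropout rate is 10%, a total of 130 participants will be needed". This is rounded up to three groups of 44, so 132 per city and 264 in all.

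The Discussion names dropout and compliance as a challenge: "Some participants might fail to complete the entire study because of business travel, tardiness, resignation and other reasons". The countermeasure it gives is explanation to participants before the start. The article states no rule for participants with some but not all weeks observed.

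**The concern.** Business travel and lateness will often cost a participant one morning and leave the other two intact. Standard repeated-measures ANOVA, with one row per person and three scores, needs all three and removes the whole row when one is missing.

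The hypothesis rests on two contrasts: adequate against inadequate breakfast, and adequate against none. A participant seen in the adequate and no-breakfast weeks but absent in the third has a complete value for the second contrast, and it would not be used.

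Two things are at stake. Precision is lost although the data were collected. The analysed set is also restricted to people who attended every week. If missing a morning is related to the breakfast condition or to performance, a completers-only comparison can be biased.

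**Working it through.** **Inputs from the article.** 117 per city before dropout; 10% dropout; 132 per city after rounding; 264 in total; power 0.80; three visits per person.

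**Assumption.** Each morning is missed independently with probability p. The article gives no such rate, so a range is shown.

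**The plan's own figure.** 117 / (1 − 0.10) = 130; 3 × 44 = 132; 2 × 132 = 264. The inflation is correct. The 117 itself cannot be reproduced, because no standard deviation or within-person correlation is given.

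**Miss rate the allowance can absorb if any missed morning removes the participant.** The expected share lost is 1 − (1 − p)³.
- Loss reaches 10% at p = 1 − 0.90^(1/3) = 3.45%.
- 132 falls to 117 at p = 1 − (117/132)^(1/3) = 3.94%, about one morning in 25.

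**Expected numbers per city.** Completers: 132(1 − p)³. Exactly two visits: 132 × 3p(1 − p)².

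| p | Share lost | Completers | Two visits | P(completers < 117) |
|---|---|---|---|---|
| 1% | 3.0% | 128.1 | 3.9 | 0.00 |
| 2% | 5.9% | 124.2 | 7.6 | 0.005 |
| 3% | 8.7% | 120.5 | 11.2 | 0.11 |
| 5% | 14.3% | 113.2 | 17.9 | 0.79 |
| 10% | 27.1% | 96.2 | 32.1 | 1.00 |

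At 1 to 3% the allowance holds in expectation, though at 3% there is about an 11% chance of falling short of 117 in a city.

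**Precision.** Count within-person information only. A complete participant contributes weight 1/3 to each of the three pairwise comparisons, and a two-visit participant contributes 1/2 to the one pair observed. The variance of a contrast from complete cases, relative to all attended visits, is therefore

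[(1 − p)³/3 + p(1 − p)²/2] / [(1 − p)³/3] = 1 + 1.5p/(1 − p).

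- p = 5%: 1 + 0.075/0.95 = 1.079.
- p = 10%: 1 + 0.15/0.90 = 1.167.

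A mixed model also recovers some between-person information. Under compound symmetry with within-person correlation 0.4, 0.6 and 0.8, the ratios become 1.09, 1.09 and 1.08 at p = 5%, and 1.20, 1.19 and 1.18 at p = 10%. A ratio of 1.09 is about 4% in standard error (√1.09 = 1.044).

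**Power.** Take 117 as giving exactly 0.80 at two-sided 0.05, so that power = Φ[(1.960 + 0.842)√(n/117) − 1.960].
- p = 5%: n = 113.2 gives 0.79 in one city; n = 226.3 pooled gives 0.97.
- p = 10%: n = 96.2 gives 0.72 in one city; n = 192.5 pooled gives 0.95.

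**The case against.** The strongest reply is that the article states no exclusion rule. It names neither a SAS procedure nor an analysis set. A long-format ANOVA with participant as a factor would keep people with two of three weeks, and covariates that can change by week, such as satiety and mood, suit such a layout better. Handling of incomplete data may also sit in an analysis plan that is not shown. This stands as a limit on the point: the loss follows from the standard form of the named method, not from a stated rule. It does not remove the point, because the method is the one thing the article does fix, and a better one is available.

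Two stronger readings are tempting, and the text supports neither.
- A reader might infer that the 10% allowance will readily be exceeded. No miss rate is given, the threshold is about 3.5% per morning under independence, and misses clustered in the same frequent travellers would remove fewer people at the same rate. The 10% may also already be meant as a per-participant non-completion rate covering travel and lateness.
- A reader might infer that one late or missed morning counts as withdrawal. The Discussion says only that some may not complete the whole study. It neither defines withdrawal nor bars return the following week. Make-up mornings are operational detail that an article need not carry.

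The power cost is also small. No separate analysis by city is stated, and pooled power remains high even at an assumed 10%.

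**Conclusion.** The point holds as a cheap improvement to the analysis. The named ANOVA, run in its standard form, would discard observed contrasts from participants with two of three weeks and limit the analysed set to full attenders, in a trial that itself foresees incomplete attendance. The amount lost cannot be determined from the article. Variance inflation of about 8 to 9% at an assumed 5% missed per morning is an illustration that rests on independent misses and compound symmetry. The power figures rest further on taking 117 as giving 0.80. No breach of the dropout allowance is shown, and its arithmetic is correct. The case rests on using the data collected and on a weaker missing-data assumption, with power a minor consideration.

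**What to change.** In Analysis strategy, fit the same model as a linear mixed model with a random participant effect, estimated by REML (available in SAS 9.2), to every attended visit. Keep breakfast condition, sex and the planned contrasts at 0.01667. Report the completers-only repeated-measures ANOVA as a sensitivity analysis.

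The cost is a wording change and no extra participants. The downside is that the mixed model relies on data being missing at random given what was observed. That is still a weaker assumption than the completers-only analysis needs, and comparing the two results shows how far the conclusion depends on who attended every week.
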